## Abstract

**Background:**

Upper limb exoskeletons are recommended to alleviate muscle fatigue, particularly in working conditions inducing musculoskeletal discomfort like overhead work. However, wearing an exoskeleton might introduce cognitive-motor interference, affecting performance. Understanding its neural impact and potential gender differences in design effects is crucial. Therefore, the aim of this study is to examine exoskeleton effects addressing cross-gender comparisons, and exploring the impact on cognitive and physical workload in real-world scenarios. The research questions address the impact of exoskeleton use on muscle synergies, upper body posture, cognitive resources, comfort/discomfort, acceptance and usability.

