### Postural discomfort

Despite all potential benefits of exoskeleton use, De Bock et al.'s (39) investigation added complexity to the understanding of discomfort, uncovering shifts and heightened frustration among exoskeleton users. Interestingly, this discomfort was accompanied by a simultaneous reduction in temporal workload, indicating a nuanced interplay of factors influencing user experience. In a separate study, Borrel Rubio and Mora Quiles (40) delved into the ergonomics of a shoulder exoskeleton during overhead assembly tasks with findings of a reduction in shoulder joint moments, indicating positive strides in enhancing user comfort. The integration of the NASA TLX questionnaire further enriched the analysis, revealing diminished perceived physical demand and a marginal reduction in mental effort. Contrary, Weston et al. (41) found slightly higher overall discomfort while using an upper-body exoskeleton during overhead tasks. Additionally, Giustetto et al. (42) found that the effect of the exoskeleton on comfort/discomfort differs in different parts of the body. For example, the exoskeleton was able to reduce discomfort in the lumbar spine region while increasing discomfort in the chest and feet. These studies therefore show that it may not be possible to increase the comfort level for all body regions.

Depending on these interdisciplinary considerations, an exoskeleton might influence cognitive and motor performance via different pathways: it would be possible that cognitive resources are given free due to physical assistance with decreased physical demands and reduced exhaustion or reflecting motor control theories, the additional use and wearing of an exoskeleton needs to be integrated into automatized movements and therefore might need more cognitive resources.

Therefore, the aim of this study is to advance our understanding of exoskeleton effects by conducting inclusive research, addressing cross-gender comparisons, and exploring the impact on cognitive and physical workload within real-world scenarios. Based on these objectives, we define the following questions with the focus on gender differences:

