### Experimental set-up/intervention

The experimental design includes two physical tasks (1. Physical Performance Task and 2. Precision Task) in four randomized conditions (with and without exoskeleton and with and without prior physical fatigue; *cf.*
Figures 1, 2):

Physical Performance Task (PILE task) at shoulder height:Participants will perform the Physical Performance Task at shoulder height, both with and without the exoskeleton. This task aimed to assess the impact of the exoskeleton on physical performance under normal working conditions.

Precision Task (nailing following the Fitts paradigm) at overhead height:The Precision Task involves overhead nailing activities following the Fitts paradigm (43, 44) (three predefined templates into which the nails must be precisely inserted.), simulating tasks requiring precision and skill. Participants will execute this task with and without the exoskeleton, allowing the evaluation of the exoskeleton’s influence on tasks demanding fine motor skills.

Randomization will be done by the online program www.randomizer.org.

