#### Physical fatigue session

A fatigue session takes place, following a randomized order, e.g., before the PILE task or before the nailing task. The fatigue session will be performed in 3 sets, with a 2-min calf raise and a 2-min front raise with weight per set, with the front raise in the second set only being performed for the second minute. The weight of the men is 5 kg and that of the women 2.5 kg. There will be a break of 60 s between the sets. During the exercise, a metronome runs at 60 bpm, and the front and calf raises are to be performed to this beat. Before the start of the fatigue session, the maximum body height will be determined individually on the anthropometer by the test person standing upright and bringing their feet into plantar flexion. This determined height should be reached during each exercise. The level of fatigue will be determined using EMG power spectral shifts (Fast Fourier Transform) in combination with a visual analog scale of peripheral fatigue.

Questionnaires on acceptance and discomfort of the conditions with exoskeleton use will be filled out after the experimental procedure.

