#### Speed accuracy trade offs (Fitts task)

The Fitts task is a standard motor control experiment in which participants move quickly between two targets of different sizes and distances (44). The aim is to assess the speed and accuracy of the target movements. The difficulty of the task is determined by a difficulty index, which is calculated based on the size and distance of the targets. The researchers manipulate the task conditions to investigate factors that influence movement time and accuracy. Key measures include movement time and error rate, which provide insight into the trade-off between speed and accuracy in motor control. The Fitts task is often used in human-computer interaction and to assess motor skills.

The Borg rating of perceived exertion is used together with the SUS and the NASA-TLX questionnaires to answer research question 1d, investigating the effects of using an upper body exoskeleton on comfort/discomfort, acceptance and ease of use during task performance.

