#### Subjective workload assessment questionnaire

The Subjective workload assessment questionnaire (NASA-Task Load Index, NASA-TLX) addresses the technical part of the experiment, capturing workload at multiple levels, regarding the interaction with the exoskeleton: mental demands, physical demands, time demands, performance, effort, and frustration (50).

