### Participant timeline

The study will be conducted over two separate days to mitigate potential carryover effects and ensure the avoidance of additional fatigue symptoms. On each day, participants will undergo the assigned conditions for both tasks in a randomized order, minimizing the impact of confounding variables. The sequence of conditions will be counterbalanced across participants to control for order effects.

First, the participants are welcomed and informed in writing and verbally about the aim and conduct of the study. This is followed by the recording of the anthropometric data and personal data. Then the preparations for the surface electromyography begin, including the application of the electrodes and the pre-tests (MVC). The suit for the Xsens sensors is then applied and a calibration is carried out. Finally, the sensor and the calibration for the fNIRS are carried out.

The first session then begins, depending on which task was selected first for the person. The person is then either fitted with the exoskeleton and begins the first task (Physical Performance Task or Precision Task) or performs this without the exoskeleton. If the fatigue protocol is already planned for the person at the beginning based on the randomization, this is carried out without the exoskeleton before the start of the task.

After completion of the first task, an individual break is taken before the second task begins. After completing both tasks, the person is asked to complete the questionnaires.

Due to the activity of overhead work, which already involves increased exertion because of the non-ergonomic posture, and the additional activity of screwing, physical fatigue may increase. Therefore, physical exertion is subjectively documented via the Borg scale (49) after each test session. Additionally, test sessions are spread over 2 days.

Individual breaks will be provided between each test session due to possible mental and physical exertion during the tests (Figure 3).

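### As written, NASA-TLX is rated only for the exoskeleton interaction, so the device's effect on its mental-demand, time-demand and frustration scales, and any gender difference in that effect, cannot be estimated

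*Protocol article*

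**What the plan says.** The aim in the Abstract (Background), repeated in the Introduction and Discussion, includes "exploring the impact on cognitive and physical workload in real-world scenarios". Under Experimental set-up/intervention, each of the two tasks is done in "four randomized conditions (with and without exoskeleton and with and without prior physical fatigue"), and the Introduction presents each participant as his or her own control.

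Four statements bear on the questionnaires:

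- **Subjective workload assessment questionnaire:** NASA-TLX is described as "capturing workload at multiple levels, regarding the interaction with the exoskeleton". Its scales are mental, physical and time demands, performance, effort and frustration.
- **Speed accuracy trade offs (Fitts task), last paragraph:** "The Borg rating of perceived exertion is used together with the SUS and the NASA-TLX questionnaires to answer research question 1d". That question concerns gender effects of using the device on comfort/discomfort, acceptance and usability.
- **Physical fatigue session, last paragraph:** "Questionnaires on acceptance and discomfort of the conditions with exoskeleton use will be filled out after the experimental procedure".
- **Participant timeline:** "After completing both tasks, the person is asked to complete the questionnaires". No condition is named.

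Borg is treated differently. Under Participant timeline, "physical exertion is subjectively documented via the Borg scale (49) after each test session", and the Statistical analysis section gives it a repeated-measures ANOVA.

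**The concern.** The effect of a device on workload is the difference between working with it and working without it. The Introduction (Postural discomfort) reports NASA-TLX from an earlier shoulder-exoskeleton study in exactly this comparative way, "revealing diminished perceived physical demand and a marginal reduction in mental effort". A rating of the interaction with the device has no counterpart when no device is worn.

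The Discussion says the study will highlight discomfort and frustration as barriers to adoption, especially for women, and the Introduction cites heightened frustration among exoskeleton users. NASA-TLX is the plan's only measure of frustration. If it exists only with the device, the study can say how frustrated women and men were while wearing it. It cannot say whether the device raised or lowered frustration, or did so differently by gender.

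**Working it through.** **1. Which instruments have a value with and without the device?**

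| Instrument | What it covers | With | Without, as written |
|---|---|---|---|
| NASA-TLX | mental, physical and time demand, performance, effort, frustration | yes | none scheduled; scope is the device interaction |
| Borg 6–20 | perceived exertion, overall and by body region | yes | yes, after each test session |
| fNIRS | cortical haemodynamics during the tasks | yes | yes |
| Precision task | time and errors | yes | yes |
| SUS, acceptance | rating of the product | yes | not meaningful |

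Borg overlaps with the physical-demand and effort scales. Mental demand, time demand and frustration have no other self-report.

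**2. What can a with-device rating identify?** Let T be the mean rating of the task without the device and D the mean change that the device causes, for women (F) and men (M).

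- Female-male difference in with-device ratings: (T_F + D_F) − (T_M + D_M) = (T_F − T_M) + (D_F − D_M).
- Female-male difference in within-person change: D_F − D_M.

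The first is one observed quantity with two unknown parts, so D_F − D_M cannot be separated out. The average device effect cannot be estimated from with-device ratings either. The second is the gender by exoskeleton contrast, and it needs both ratings.

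**3. Is T_F = T_M a safe assumption?** The protocol gives no reason to think so. The PILE task starts at 4 kg for women and 6 kg for men, and the front-raise weight in the fatigue session is 2.5 kg and 5 kg. The work itself differs by gender before any device is worn.

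**4. Illustration only.** The plan states no figure to reproduce. Inputs: 36 per gender (Sample size section), two-sided alpha 0.05. Assumed: a two-sample t test on with-device ratings, no gender-specific device effect (D_F = D_M), and a standardised bare-task difference d = (T_F − T_M)/SD. Noncentrality = d × √(36/2).

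- d = 0.3: 0.3 × 4.243 = 1.27, so the test is significant in 24% of trials.
- d = 0.5: 0.5 × 4.243 = 2.12, so the test is significant in 55%.
- d = 0: 5%, the nominal rate.

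With both ratings the bare-task difference cancels. The SD of the change relative to a single rating is √(2(1 − ρ)), where ρ is the within-person correlation (not given in the documents).

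- ρ = 0.8: √0.4 = 0.63.
- ρ = 0.6: √0.8 = 0.89.
- ρ = 0.5: 1.00. Below 0.5 the change is noisier than a single rating.

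Removal of the bias does not depend on ρ; the gain in precision does.

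**The case against.** **The restriction is inferred.** No sentence says that NASA-TLX is given only in exoskeleton conditions. The Physical fatigue session section limits questionnaires on acceptance and discomfort and does not name workload. The Participant timeline wording is open enough to allow a rating on every occasion. The time-schedule figure is not shown, and a journal article leaves detail to the full protocol. This stands in part: the investigators may intend to give NASA-TLX throughout. But the article does more than leave the schedule out. It defines what the instrument rates, and that definition has no meaning without the device. For Borg it states rating after each session; for NASA-TLX it does not. If the questionnaire is in fact given in every condition, its description is wrong and still needs changing.

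**The workload aim is covered elsewhere.** A reader might infer that perceived workload has no comparator at all, or that fNIRS is the only evidence on cognitive load. Neither is supported. Borg gives perceived exertion in both conditions. Precision-task time and errors stand beside fNIRS in both, and the Discussion predicts lower working accuracy along with more prefrontal activation.

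**No research question asks for the change in self-reported mental load.** Cognitive resources are assigned to fNIRS, and NASA-TLX to question 1d. That is correct. However, the same sentence that assigns NASA-TLX to 1d says it is there to investigate effects of using the device, and that needs a comparator too.

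**The percentages are not the plan's.** This stands. The bare-task difference, the correlation and the t test are all assumed, and the Statistical analysis section names no test for NASA-TLX.

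**Conclusion.** The point holds for NASA-TLX and no further. As the article is written, the exoskeleton's effect on self-reported mental demand, time demand and frustration, and any gender difference in that effect, cannot be estimated. A comparison of women's and men's with-device ratings would confound rating of the task with effect of the device. The conclusion rests on reading the questionnaire's description as its scope, which the other sections favour but do not state outright.

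The overall workload aim is weakened, not defeated, because exertion, cortical activation and precision-task performance can be compared with and without the device. The documents give no figure for the size of the gender bias. The 24% to 55% range shows what an assumed difference of 0.3 to 0.5 SD would do in one assumed test, and it should not be read as the error rate of this trial. Because the without-device conditions are already in the design, this is a cheap improvement worth making before data collection.

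**What to change.** 1. Give the six NASA-TLX items after each condition, with and without the exoskeleton, and word the stem for the task just performed rather than for the device.
2. Analyse the scores by repeated-measures ANOVA, as for Borg, with gender by exoskeleton as the test of interest.
3. Keep SUS and the acceptance questions for exoskeleton conditions only, where they make sense.
4. Align the Subjective workload assessment questionnaire, Physical fatigue session and Participant timeline sections so that they state the same scope and timing.

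**Cost:** six further items, an estimated one to two minutes, per without-exoskeleton condition. With two without-exoskeleton conditions (fatigued and not), one rating per condition adds 2 × 6 = 12 items, about 2 to 4 minutes per participant. Rating each task separately doubles this to 24 items, about 4 to 8 minutes. If the present intention is a single with-device rating at the end, the with-device conditions also gain some items. No new instrument or staff is needed.

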**Methods:**

The cross-sectional study integrates a multifactorial mixed-measure design. Participants are grouped by gender (female vs. male) and working condition (with vs. without exoskeleton). Motor performance and underlying neuronal correlates (fNIRS) will be analyzed. Based on an *a priori* sample size calculation, 80 participants (40 female/40 male) will be recruited. Working performance will be assessed by 1. Physical Performance Task (PILE task) and 2. Precision Task (following the Fitts paradigm), while body postures will be monitored with an Xsens motion capture system. Brain activation will be captured with an fNIRS system comprising 32 active optodes. Postural comfort/discomfort, acceptance, and usability will be reported via standardized questionnaires.

**Discussion:**

The study will gain insights into potential gender differences in exoskeleton use and will contribute to designing and optimizing the implementation of exoskeletons by considering muscle synergies, movement variability and cognitive resource allocation. Additionally, the study also highlights user discomfort, a crucial factor that could impede widespread adoption, particularly among females, in real-world scenarios.

## Introduction

The escalating demands within industrial settings, characterized by increased production volumes, repetitive tasks, and constrained postures, have led to a rising prevalence of musculoskeletal complaints, contributing to the emergence of musculoskeletal disorders (MSDs) (1). Musculoskeletal disorders, categorized by Van Eerd et al. (2) as inflammatory and degenerative conditions, pose significant challenges, particularly in the construction industry, where nearly 27% of employees faced such issues in 2017. The associated production downtime costs due to work absenteeism in Germany alone amounted to 17.2 billion euros (3).

Tasks performed at or above head height, common in industrial settings, pose substantial challenges and frequently lead to these MSDs. The use of exoskeletons, wearable external mechanical support structures designed to enhance user performance offer flexibility and performance enhancement, potentially reducing physical strains and preventing work-related diseases, especially MSDs (4). The application of exoskeletons involves human-machine interaction (HMI), encompassing both psychological and physical aspects. While previous studies have demonstrated positive effects of exoskeletons in terms of assistive support, there are challenges related to user muscular demands, altered posture, cognitive-motor interaction (CMI), and discomfort.

To gain more insights into these aspects, comprehensive approaches integrating the analysis of muscle activities and changes in muscle synergies in a combined measurement set-up including also kinematic data of body posture as well as brain dynamics to analyze CMI and the subjective impression of postural comfort or discomfort should be used. Following this idea, we summarized the state of the art of the main aspects of specific interacting parts of this approach in the next sections. These are: (1) Muscle activity and muscle synergies, (2) Movement/posture, (3) Cognitive-motor interference and (4) Postural Discomfort.

### Muscle activity and muscle synergies

In recent studies on (upper-body) exoskeleton use, researchers have already explored various aspects related to muscle activity, but with varying results (5–10). The need to support the back and shoulder muscles is particularly important for overhead and lifting activities (5–11). Studies have shown a reduction in muscular activation associated with exoskeleton use in the *M. deltoideus*, *M. Biceps brachii* during overhead tasks, and *M. Triceps brachii* (7, 8; 11). Different effects are observed in *M. Brachioradialis* and *M. pectoralis* major depending on the task (5, 8), and mixed results are presented regarding the activation of the *M. trapezius* but a consistent reduction in the M. Infraspinatus during exoskeleton-assisted overhead tasks (12, 13). Furthermore, the effectiveness of upper body exoskeletons in supporting back muscles presents varied outcomes for the *M. Latissimus dorsi* and *M. rectus* abdominis (9, 14, 15).

Regarding the interplay of the different muscle groups during exoskeleton use the muscle synergy extraction can be used to reduce degrees of freedom within high-dimensional datasets (16). After the initial proposal of the concept by Bernstein (17), several groups demonstrated that the central nervous system might simplify complex movements through the grouping of co-activated muscles into modular organizational units, called muscle synergies (18–20). A muscle synergy can be defined to be a vector specifying relative levels of muscle activation, with the absolute level of activation being modulated through a single neural command (21).

Among methodologies tested for muscle synergy extraction from surface electromyography data, non-negative matrix factorization (22) became generally accepted as the most suitable algorithm in locomotion tasks (23). Changes in muscle synergy number, synergy composition, or their respective activation profiles, has been observed within a wide range of subjects, e.g., due to cortical lesions (24), knee osteoarthritis (25, 26), or after total knee arthroplasty (27, 28).

Within the context of rehabilitation of stroke survivors, changes in muscle synergies have been also reported through the use of an active ankle-foot exoskeleton (29) and arm weight support (30). In an industrial setting with healthy participants, only one study investigated the effect of an active exoskeleton: The use of an active lumbar support exoskeleton during repetitive stoop lifting induced alterations within the synergies’ activation profiles, but only minimal alterations within the relative levels of muscle activation (31). No studies have yet investigated the effect of an industrial upper limb exoskeleton on muscle synergy composition, yet understanding these effects can play a vital role in understanding the complex interplay between user and device.

In addition, limited evidence exists regarding gender differences in muscle activity during exoskeleton use, with some studies indicating higher muscular demands and discomfort for females during overhead and carrying tasks (6, 32, 33). Moreover, to our knowledge, no additional research has specifically examined gender disparities in the use of upper body exoskeletons for tasks involving overhead movements or carrying/lifting activities.

